## Procedure for withdrawal of patients from the cohort

Enrolled patients will be withdrawn from the cohort for the following reasons:

1. Movement out of the study area for > 60 consecutive days
2. Inability to be located for > 60 consecutive days
3. Withdrawal of informed consent
4. Development of any serious adverse event that requires a withdrawal from study
5. Failure to achieve an adequate clinical response after treatment with quinine plus clindamycin except if it was a severe malaria attack requiring parenteral quinine therapy.
6. Unable to comply with the study schedule and procedures
7. Diagnosis of a serious chronic disease requiring frequent medical care.

If a patient is withdrawn for reasons # 1, 2, or 3, we will be unable to perform any additional study procedures, and will not plan to obtain any follow-up tests. If a patient is withdrawn for reasons # 4, 5 or 7, because a serious health problem developed plans to obtain appropriate follow-up tests will be individualized to each patient. If the patient is withdrawn for reason # 6, plans to obtain appropriate follow-up tests, will be individualized to each patient, depending on the health status of the patient at the time of withdrawal, and the willingness of the participant and their parent/guardian to proceed with additional testing.

- All study withdrawals should be recorded by the Investigator in the appropriate pages when considered as confirmed;
- If possible, the patients are assessed using the procedures normally planned on D28 if withdrawal before D28 or using the procedures planned on D42 if withdrawal between D28 and D42.

The Investigator should make every effort to contact the patient, to identify the reason why he/she failed to attend the visit, and to determine his/her health status, including at least his/her vital status.

Patients who did not complete the study and for whom no endpoint data are available will be considered as lost to follow-up. The statistical analysis plan will specify how these patients lost to follow-up for their primary endpoints will be considered.

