## Study rationale

This phase IV study will validate the efficacy and safety of Coarsucam® in children under 5 years old in a high transmission area. Effectiveness, compliance and safety of Coarsucam® in repeated administrations for the treatment of consecutive episodes of uncomplicated malaria, in more real conditions of use, (unsupervised intakes) will also be validated. Coarsucam® will be compared to the fixed-dose combination containing an artemisinin derivative currently recommended as first line treatment by Uganda’s health authorities, for this reason*,* patients must be weighting at least 5 kg

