## Concomitant treatment

### Prohibited medication

Any antimalarials or antibiotic with antimalarial activity (erythromycin or other macrolides, co-trimoxazole or other sulphonamides, any tetracycline including doxycycline, and quinolones, clindamycin…) is not authorised during the study follow up of 42 days. Intake of these drugs leads to withdrawal of the patient from the ongoing active follow up. However, the patient will be kept in the passive follow up and when presenting with another clinical malaria episode fulfilling the inclusion/exclusion criteria, another active follow up can be started. There are no disallowed concomitant therapies during the passive follow up.

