## Treatment accountability and compliance

For the first attack, each dose of the study treatment will be administered by a study nurse, and the patient will be monitored for 30 minutes after administration. If the patient vomits or rejects the treatment within the 30 minutes, the same dose will be re-administered. In the event of repeated vomiting, a replacement treatment will be given as discussed in 9.7.3. Study participants may choose to either be hospitalised (retained at the clinic) for administration of study medications or to commute from home. Participants will be reimbursed for transport to and from the clinic and for meals or other incidental expenses if they are hospitalised for treatment administration. Amounts for reimbursement will be based on the current rates for transport, meals and incidental expenses. Home visitors shall actively follow patients who do not come for scheduled appointments.

For the repeat attacks the 1st intake will be administered at the study clinic and the other intakes will be unsupervised. At day 3, the patient will give the blister to the study nurse who will check the number of remaining tablets in the returned blister. The parent/guardian will inform the clinical team member of any event related to these intakes. In case of vomiting of an unsupervised intake within the 30 minutes, the patient will visit the study clinic where the same dosage will be administered again.

The study nurse shall record the information on the appropriate CRF page. The Monitor in charge of the study then checks the CRF data by comparing them with the Investigational Product which he/she has retrieved and treatment log forms. All steps will be taken to ensure that patients receive treatment in compliance with the protocol.

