## Compliance for the 2nd and following attacks

Compliance shall be determined by

- Checking the remaining tablets in returned blisters at D3 by patients. The investigator will count the remaining tablets and in case of discordance the investigator will ask for the reason.
- Dosage of plasma level of desethyl-amodiaquine or lumefantrine. At D3 and D7, a vaccinostyle will be used to collect blood from fingerpick onto filter paper. It will be an exploratory assessment that could be preformed in case of failure or significant intolerance

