# Handling of patient TEMPORARY OR DEFINITIVE TREATMENT DISCONTINUATION AND OF PATIENT STUDY DISCONTINUATION

The investigational product should be continued whenever possible. Any IP discontinuation should be fully documented in the CRF. In any case, the patient should remain in the study as long as possible.

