## Consequence

Patients who have been withdrawn from a followed-up attack can be maintain or not in the cohort, for potential next attacks, according to investigator’s judgment. Their randomization number of patients not maintained in the cohort must not be reused.

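### Section 12.2 makes an undefined inability to comply a mandatory ground for leaving the 2-year cohort, which can selectively thin the later-attack comparisons

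*Protocol*

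**What the plan says.** The list in section 12.2 opens with mandatory wording: "Enrolled patients will be withdrawn from the cohort for the following reasons". Reason 6 reads "Unable to comply with the study schedule and procedures". Reasons 1 and 2 (moving away, cannot be located) each carry a 60-day threshold. Reason 6 has no threshold, definition or decision procedure.

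Three other places bear on whether a child stays:

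- The opening of section 12: "In any case, the patient should remain in the study as long as possible".
- Section 9.7.1, on a child who takes a prohibited antimalarial or antibiotic and so leaves the active follow-up of that attack: "However, the patient will be kept in the passive follow up".
- Section 12.3, on children withdrawn from one attack: they "can be maintain or not in the cohort, for potential next attacks", according to the investigator's judgment.

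The repeat-attack phase is meant to study use outside supervision. Section 5.4 says that effectiveness, compliance and safety of repeated courses "in more real conditions of use, (unsupervised intakes) will also be validated". Section 9.9 sets the dosing conditions: "For the repeat attacks the 1st intake will be administered at the study clinic and the other intakes will be unsupervised". Section 10.3 says what follows an unexpected tablet count: "The investigator will count the remaining tablets and in case of discordance the investigator will ask for the reason".

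**The concern.** Reason 6 acts after randomisation and turns on how well a family copes with the protocol. How families cope with unsupervised treatment is part of what the repeat-attack phase compares. Section 6.2 lists compliance and effectiveness in repeated attacks as between-arm comparisons. Section 5.3 gives a reason to expect a difference, since it notes adherence concerns about the comparator's twice-daily dosing and its need for fatty food.

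A child who leaves the cohort supplies no later attacks, and no choice of analysis set can restore data that were never collected. Three planned analyses depend on later attacks:

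- the evolution of each patient's compliance over 2 years (section 14.5.2);
- the repeated-measures model with attack rank, treatment and their interaction (section 14.5.3.2);
- the number of attacks per child and the mean delay between attacks (section 10.1.2).

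If less adherent children leave preferentially, the group behind these analyses becomes more adherent with each attack. The arm with more non-adherence loses more such children, so the arms would tend to look alike.

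**Working it through.** **1. Does reason 6 reach drug intake?** The text neither says so nor excludes it. For exclusion: it names schedule and procedures, not tablets, and section 10.3 attaches only a query to a discordant count. For inclusion: returning the blister and booklet on D3 is a listed procedure (section 13.2.3), and Appendix 7 defines compliance broadly, as adherence to all research requirements. Both readings are open to a site. Even on the narrow reading of missed visits, the families removed are those who struggle with the protocol, and less adherent families are plausibly among them.

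**2. Is the loss forced by circumstances?** For reasons 1 to 3, section 12.2 says that no further study procedures will be possible. For reason 6 it foresees follow-up tests, depending on the child's health and the family's willingness. Some of these children can therefore still be reached, and it is the rule itself that ends their cohort data.

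**3. What stays in the data?** Compliance is calculated for each attack on the safety and ITT populations (section 14.5.2). ITT membership needs one dose, apart from double vomiting or rejection at the first intake (section 14.4.1). Incomplete unsupervised intake becomes visible only when the blister is counted at D3, so the attack that reveals it is already recorded.

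**4. How large could the attenuation be?** The protocol gives no figure to reproduce. Its sample size of 174 evaluable patients per group concerns the supervised first attack. The following is an illustration, and every input is an assumption:

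- mean risk of incomplete intake per unsupervised attack: 10% in one arm, 20% in the other;
- variation between children: Beta distribution with concentration 2, that is Beta(0.2, 1.8) and Beta(0.4, 1.6);
- six unsupervised attacks per child;
- a share w of non-adherent attacks followed by cohort withdrawal, after the blister count.

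Simulating 200,000 children per arm gives these between-arm differences, in percentage points:

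| w | first unsupervised attack | pooled over six | sixth attack |
|---|---|---|---|
| 0 | 10 | 10 | 10 |
| 0.10 | 10 | 9.5 | 9.0 |
| 0.25 | 10 | 8.6 | 7.2 |
| 0.50 | 10 | 7.6 | 5.2 |
| 1.00 | 10 | 6.2 | 2.9 |

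The extreme row can be checked by hand. With w = 1, a child still present at attack k has had k − 1 adherent attacks, so the mean risk at attack k is a/(2 + k − 1), where a is the first Beta parameter. At k = 6 this is 0.2/7 = 2.86% and 0.4/7 = 5.71%, a difference of 2.86 points, which agrees with the simulated 2.9.

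The direction is the same in every row with w above 0: the difference shrinks, more so at later attacks, and does not reach zero.

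**The case against.** The strongest reply is that reason 6 concerns attendance. Section 12.2 goes on to discuss patients who did not attend a visit, section 12.1.1 does not list missed doses as a ground for stopping treatment, and section 10.3 treats a discordant count as something to ask about. The repeat-attack visits are the same in both arms, so on this reading the documents give no reason for withdrawal to differ by arm. Home tracing of missed appointments (section 9.9) and home visits after 30 days without contact (section 13.3) also work against such loss. Eligibility already asks for ability and agreement to comply (sections 8.2.1 and 8.2.2).

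Much of this stands. It makes the size of the effect uncertain, and equal visit schedules weaken the argument for arm-dependent withdrawal. It does not supply a definition, and it does not make a mandatory rule optional.

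The alleged conflicts are also softer than outright contradictions. Section 12's opening principle is qualified, and section 9.7.1 deals with a different event. Still, a child who takes a prohibited drug stays under observation while one whose family struggles with the schedule does not, and the mandatory wording of 12.2 and the discretion in 12.3 give a site no clear rule.

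A reader might infer that repeat-attack compliance and effectiveness are measured only in compliant children, or that the difference between arms vanishes. The documents do not support either. Only the per-protocol set selects on compliance, and the attack that reveals incomplete intake is kept in the safety and ITT sets. A vanishing difference needs the withdrawn children to have contributed no unsupervised attack at all, which cannot happen when incomplete unsupervised intake is what triggers withdrawal.

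**Conclusion.** The point holds in a limited form. Section 12.2 contains a mandatory, undefined withdrawal rule, applied after randomisation, that can remove less adherent families from later attacks. If it is used that way, the secondary comparisons that rely on later attacks lose data selectively, and an adherence-related difference would probably be attenuated but not abolished. The size depends on how often the rule is applied, which the protocol leaves open. The range of 9.5 to 6.2 points pooled, from a true 10, rests wholly on the assumed inputs.

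The primary non-inferiority comparison is not affected by this mechanism, because first-attack doses are given under observation. How children lost before their primary endpoint are handled is left by section 12.2 to the analysis plan and is not part of this point. This is worth correcting for the declared repeat-attack objectives; it is not a threat to the main conclusion.

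**What to change.** Remove reason 6 as a ground for ending cohort follow-up. Alternatively, define it and state that missed visits or incomplete unsupervised intake alone do not end data collection. Keep these children in passive follow-up, analyse them in their randomised arm, and count their attacks and compliance. Handle non-compliance through the per-protocol status of the attack concerned. A family that wishes to leave is already covered by reason 3, withdrawal of consent.

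Reconcile section 12.2 with the opening of section 12, with 9.7.1 and with 12.3, so that it is clear when leaving the cohort is required, when it is a matter of judgment, and when only the current attack's active follow-up ends. Check that the per-attack agreement to comply in section 8.2.2 cannot be used to the same effect.

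The cost is a few lines of text. The downside is that some children with more missed visits, and so less complete data per attack, stay in the cohort. This concerns data retention only and implies nothing about how any attack should be treated.

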## Consequence

Patients who have been withdrawn from a followed-up attack can be maintain or not in the cohort, for potential next attacks, according to investigator’s judgment. Their randomization number of patients not maintained in the cohort must not be reused.

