**During the total follow up of the cohort**

To compare the two groups of treatment in terms of:

- Treatment incidence density
- Impact of repeated treatment on clinical and biological tolerability
- Impact on anaemia
- Impact on Hackett score

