### Biological tolerability

- Haematology and biochemistry will be routinely performed on days 0, 7, and 28. Haematology and biochemistry will be repeated on Day 14 and 42 if results are abnormal on Day 7 and Day 28 respectively. Haematology and biochemistry may be performed on any other day if the clinician feels results are necessary for patient management. An additional haemoglobin evaluation will be performed on day 3 from blood collected by a fingerprick and read using a portable spectrophotometer (Haemacue). Blood samples for haematology and biochemistry will be collected from patients by venipuncture. About 2 mls of blood will be drawn from each patient for biochemistry/haematology during these visits. Additional venipunctures will be performed, as appropriate, for follow-up of adverse events.

Laboratory analyses are described in Appendix 6

- Haematological parameters: haemoglobin, platelets, leukocytes, neutrophils.These parameters will be measured by a complete blood count and assay of haemoglobin and measurements shall be done by a haematology coulter
- Biochemical parameters: blood creatinine, total bilirubin, ALT. These parameters will be measured according to the enzyme assay methods for each parameter.

Note: Any abnormal laboratory (at least grade 3) value will be immediately rechecked, in case of confirmation all investigations to know the reason will be performed and the patient will be followed until normalization. The possible withdrawal of the patient from the cohort will be taken by the investigator.

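### Sections 12.3 and 10.2.2 let the investigator end a child's 2-year cohort follow-up by judgement, in conflict with 9.7.1, 12 and 12.2, so exit can depend on outcome in the secondary comparisons

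*Protocol*

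**What the plan says.** Two places give the investigator an open decision on cohort membership. Section 12.3 (Consequence) says: "Patients who have been withdrawn from a followed-up attack can be maintain or not in the cohort, for potential next attacks", according to the investigator's judgement. Section 10.2.2 (Biological tolerability) says "Any abnormal laboratory (at least grade 3) value will be immediately rechecked"; if the value is confirmed, the cause is investigated and the child is followed until normalisation. It then adds: "The possible withdrawal of the patient from the cohort will be taken by the investigator".

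Three other places point the other way.

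- 9.7.1 (Prohibited medication), on antimalarials and antibiotics with antimalarial activity taken during the 42 days: "Intake of these drugs leads to withdrawal of the patient from the ongoing active follow up". The child is nevertheless retained: "the patient will be kept in the passive follow up and when presenting with another clinical malaria episode fulfilling the inclusion/exclusion criteria", a new active follow-up can begin.
- The opening of section 12: "In any case, the patient should remain in the study as long as possible".
- 12.2 lists seven reasons for withdrawal from the cohort. Neither leaving one attack nor a grade 3 laboratory value is among them. The only adverse-event reason is a serious adverse event that requires withdrawal.

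The objectives for the whole cohort follow-up (6.2) are treatment incidence density, "Impact of repeated treatment on clinical and biological tolerability", anaemia and the Hackett score.

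**The concern.** A child who leaves the cohort contributes nothing further to attack counts, intervals between attacks, anaemia or spleen score. That does little harm if exit is unrelated to outcome. Here some of the events that open the decision are tolerability outcomes or signs of intolerance, and the decision has no criteria. Later attacks may therefore come from a cohort depleted of the children who tolerated treatment worst.

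Section 5.4 says that the safety of repeated administration will be validated, so these comparisons, though secondary, carry part of the trial's purpose. An analysis plan can describe such exits, but it cannot recover data that were never collected. The one relevant deferral to the analysis plan, in 12.2, concerns patients lost to follow-up for their primary endpoints.

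**Working it through.** No figure in the protocol depends on this point, so there is none to reproduce. The check sets the sections side by side and adds an illustration with assumed inputs.

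**1. The rules compared**

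| Situation | Discretionary rule | Other rule | Relation |
|---|---|---|---|
| Withdrawn from an attack for a prohibited drug | 12.3: keep or drop | 9.7.1: kept in passive follow-up | Direct contradiction |
| Withdrawn from an attack for another reason, e.g. repeated vomiting or rejection (9.7.3) | 12.3: keep or drop | Section 12: retain as long as possible; 12.2: not a listed reason | Conflict with the general rule; unlisted exit route |
| Confirmed laboratory value of grade 3 or more | 10.2.2: investigator decides | Section 12 and 12.2, as above | Same, with partial overlap for ALT (see the objection) |

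**2. Are the triggers related to the outcomes?**

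- Repeated vomiting or rejection is a recorded reason of withdrawal (9.7.3), and clinical tolerability is an outcome.
- Haemoglobin below 7.0 g/dL is grade 3 in both age bands that apply to this cohort (Appendix 3), while 8.2.2 admits children to an attack from 5.0 g/dL. A child at 5.0 to 6.9 g/dL is therefore eligible and can also meet the 10.2.2 trigger. Anaemia at D0 of each episode is a cohort outcome (10.1.2).
- Neutrophils below 400/mm3 reach grade 3 (250 to 399) or grade 4 (Appendix 3). The same threshold defines an event of special interest in 11.8.
- 14.5.4.2 compares the number of patients with abnormal values by grade over the 2 years. 10.2.2 allows those with the highest grades to leave.

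**3. What a common dropping rule does to a comparison between arms**

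All inputs are assumed. Let s be the share of intolerant children in an arm and q the fraction of them dropped after attack 1. Let rI and rT be the event risks per repeat episode in intolerant and tolerant children. Each retained child is taken to have the same number of attacks, and no tolerant child is dropped.

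Rate per repeat episode = [s(1−q)rI + (1−s)rT] / [s(1−q) + (1−s)]

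Take rI = 30%, rT = 5%, s = 15% in arm A and 5% in arm B.

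- q = 0: A = 0.15×0.30 + 0.85×0.05 = 8.75%; B = 0.05×0.30 + 0.95×0.05 = 6.25%; difference 2.5 points.
- q = 0.5: A = (0.075×0.30 + 0.0425)/0.925 = 7.03%; B = (0.025×0.30 + 0.0475)/0.975 = 5.64%; difference 1.4 points.
- q = 0.75: 6.06% and 5.32%; difference 0.7 points.
- q = 1: 5% in both arms; difference 0.

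Range over other assumed inputs, with rT = 5% (differences in points):

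| s in A / B | rI | q = 0 | q = 0.5 | q = 0.75 | q = 1 |
|---|---|---|---|---|---|
| 15% / 5% | 50% | 4.5 | 2.5 | 1.3 | 0 |
| 10% / 5% | 30% | 1.25 | 0.67 | 0.35 | 0 |
| 10% / 5% | 50% | 2.25 | 1.21 | 0.63 | 0 |
| 10% / 10% | 30% | 0 | 0 | 0 | 0 |

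In the last row the difference stays at zero, but the rate in both arms falls from 7.5% to 5% as q goes from 0 to 1. The same q is applied in both arms throughout, so the shrinkage needs no knowledge of treatment.

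**The case against.** The strongest reply is that these are permissive clauses sitting beside other rules, and that the protocol already protects follow-up in several ways. Much of it stands, and it limits what a reader may infer.

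- *That 9.7.1 keeps every child who leaves an attack.* It does not. It covers only prohibited medication, a trigger that is not itself drug intolerance. The direct contradiction goes no further than that.
- *That the 12.2 list is closed.* It does not say so, and reasons 4 and 6 already involve judgement. There is also overlap: ALT reaches grade 3 at 10 times ULN, and 11.3 names an asymptomatic rise to that level as an example of a medically important serious event, so such a case could fall under reason 4. Even so, a list of exit reasons loses much of its force if 12.3 adds a route without criteria.
- *That attack withdrawals are mainly due to intolerance, or that stopping drug is merged with ending data collection.* Neither is supported. 12.1.1 lists criteria for stopping treatment, and 12.1.2 keeps those children under follow-up to D42 or until an adverse event resolves or stabilises, whichever is later. 9.7.4 likewise follows failures to D42. No frequencies are given. These provisions protect the current attack, however, and not the rest of the 2 years.
- *That intolerant children will in fact be removed.* The text permits this but does not require it; q may be zero.
- *Blinding.* 9.2.2 blinds the investigators who evaluate patients. That limits decisions driven by treatment arm. It does not prevent selection on toxicity, which they can see.

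**Conclusion.** The concern holds as a conflict between sections that permits outcome-related exit from the cohort. 12.3 directly contradicts 9.7.1 for prohibited-medication withdrawals. 12.3 and the 10.2.2 note both sit badly with section 12 and 12.2. The comparisons exposed are the secondary 2-year ones: attack count, interval between attacks, anaemia, Hackett score and tolerability under repeated treatment.

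Neither the size nor the direction of any bias can be computed from the document. The illustration shows only a mechanism, under assumed shares, risks and dropping fractions. A reader might infer from it that a real difference will be hidden, or that safety will seem to improve with repeated use; the document does not establish either. The primary D28 analysis rests on each child's first attack and does not depend on retention for later attacks. The sponsor should correct this, but the primary conclusion does not hang on it.

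**What to change.** Reconcile 9.7.1, 10.2.2, the opening of section 12, 12.2 and 12.3 so that they state one rule: leaving the follow-up of one attack, or stopping study drug, does not by itself end data collection. The child stays in the existing passive follow-up, which supplies attack counts and dates and the findings at clinic visits that take place anyway, and the treatment actually received is recorded. Tabulate cohort exits by arm, reason and attack number. Whether study drug is given again remains the investigator's decision; no clinical rule is proposed here.

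The cost is mainly wording. Consent is obtained once and covers the whole period (8.2.1, 15.3), and the clinic already provides routine care free of charge (13.5). No new scheduled tests are needed.

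Two downsides remain. Some follow-up will be off study drug and must be labelled so. And 10.2.3 compares repeat-treatment tolerability per episode treated with a study drug, so a child kept in the cohort but no longer given it still adds no episodes there. The change restores the other 2-year outcomes; the tolerability comparison should be read alongside the exit table.
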